#### Functional evaluations

The following functional evaluations will be performed by a blinded physiotherapist preoperatively and at 2, 4, 6, 12, 26 and 52 weeks after TKA. Some measures will also be assessed at day 2 postoperatively; however, these measures will be taken by an unblinded ward physiotherapist. Functional evaulations are illustrated in Fig. 2.

**Fig. 2 Fig2:**
[figure not shown]
KangaTech set-up. **a** Hip abduction: for bilateral hip abduction testing, the participant will also be seated, with the knee flexed at 15° and lumbo-pelvic-hip complex flexed at 60°. The dynamometry pad will be positioned at the level of the lateral femoral condyles. **b** Knee extension: unilateral knee extension performed with participants seated, their knee at 45° flexion and lumbo-pelvic-hip complex at 60° flexion. The dynamometry pad will be positioned at the level of the lateral malleolus at right angles to the shank/tibia. Each thigh will be secured to the seat with a belt above the level of the surgical incision (> 10 cm above the supra patella border). **c** Knee flexion: unilateral knee extension performed with participants seated, their knee at 45° flexion and lumbo-pelvic-hip complex at 60° flexion. The dynamometry pad will be positioned at the level of the lateral malleolus at right angles to the shank/tibia. Each thigh will be secured to the seat with a belt above the level of the surgical incision (> 10 cm above the supra patella border). **d** Set-up alone at Flinders Private Hospital for use in this study

##### Joint range of motion and the Visual Analogue Scale for Pain in flexion and extension

In a seated position, active joint ROM in flexion and extension will be measured using a standard goniometer. Furthermore, pain at end-of-range flexion and extension will be measured using the Visual Analogue Scale (VAS) for Pain. Recovery in knee ROM has been found to plateau 12 months after TKA, therefore end-of-study has been selected to be 12 months postoperatively [28]. Both measures will also be assessed at day 2 after TKA.

##### Isometric knee extensor strength, flexor strength and bilateral hip abduction

Hand-held isometric [29–32] and isokinetic [30, 31, 33, 34] dynamometry has previously been used to safely and effectively measure maximal quadricep and hamstring muscle strength in OA and TKR populations. In the present study, a customised fixed-frame portable dynamometry hardware and software system (KangaTech, Melbourne, Australia) will be used to measure maximum voluntary isometric strength of the quadriceps, hamstring and hip abductor muscle groups of each participant.

Maximum voluntary isometric contraction (MVIC) will be tested for the hip abductors, knee extensors and knee flexors in a seated position to maximise participant comfort. Unilateral knee extension and flexion tests will be performed with participants in a seated position with their knee at 45° of flexion and with their lumbo-pelvic-hip complex at 60° of flexion. The dynamometry pad will be positioned at the level of the lateral malleolus at right angles to the shank/tibia. Each thigh will be secured to the seat with a belt above the level of the surgical incision (> 10 cm above the supra patella border). For bilateral hip abduction testing, participants will also be seated, with the knee flexed at 15° and lumbo-pelvic-hip complex flexed at 60°. The dynamometry pad will be positioned at the level of the lateral femoral condyles.

Participants will perform each test in a randomly selected order after having had three gradually ramped practice/warm-up trials. During these trials, participants will be asked to produce an isometric contraction at 20%, 50% and 80% of their perceived maximum effort for 3 s. Participants experiencing any discomfort that is unusual and/or with an associated pain score of > 3/10 (measured by the VAS – Pain) above their resting level of pain will be asked not to proceed beyond this level of force or effort. In this case, the pain limited MVIC will be recorded.

Participants that warm up without the forementioned symptoms will proceed to 2 × 5 s MVIC test trials for each test. Participants will again be advised to limit force in the presence of discomfort. Time allowed for recovery between all tests will be 20 s.

##### Balance test, knee circumference and thigh circumference

This balance test will be performed in a single-leg standing position, with eyes open. The ability to maintain balance in this position will be recorded in seconds.

The participant’s knee and thigh circumference will be measured using a regular tape measure. The measurements will be taken at two points, specifically at the superior pole of the patella and 15 cm above the superior pole of the patella. Both measures will also be assessed at day 2 after TKA.

##### Clinical performance tests

Clinical performance tests, including the 30-s Chair-Stand Test and the 4 × 10 m Fast Paced Walk Test, will be performed in accordance with the Osteoarthritis Research Society International (OARSI) Report guidelines [35]. The tests will be conducted preoperatively and at 2, 4, 6 and 12 weeks, 6 and 12 months postoperatively.

#### Economic evaluation

An economic evaluation assessing the relative cost-effectiveness of the Maxm Skate rehabilitation device compared to standard care will be conducted.

This analysis will take the form of an economic evaluation comparing the relative cost-effectiveness analysis of the Maxm Skate rehabilitation device to standard care using data collected during the trial. The primary outcome will be the incremental cost per unit increase in knee ROM while a secondary outcome will be the incremental cost per quality-adjusted life year (QALY) gained over the period of the primary study and based on the EQ-5D-5 L. As an Australian scoring algorithm for the EQ-5D-5 L is not yet available, the UK value set and scoring algorithm [36] will be used to convert the individual responses to the EQ-5D-5 L at each time point. Resource use associated with each trial arm will be combined with unit costs for these resources in order to estimate total costs in the trial. Costs will be estimated from a societal perspective (to include costs borne by private hospitals and insurance providers, private patients and social care service providers). Resource use data will include a number of tests, treatments and investigations undertaken during in-hospital visits, the frequency and duration of in-hospital admissions, over the counter medication, lost productivity, social care services, as well as quantity and type of consumables and equipment used. Resource use data to capture patient-specific costs incurred will only be collected after discharge, using a resource use questionnaire that will be administered at 2, 4, 6, 12, 26 and 52 weeks. Resource unit costs will be derived from hospital finance departments and supplemented, where necessary, by information from published source including the Australian Bureau of Statistics and Australian Refined Diagnosis Related Groups (AR-DRG) cost weights. Confidence intervals will be presented around the incremental cost-effectiveness ratios and cost-effectiveness acceptability curves for varying threshold values of cost-effectiveness will also be presented [37]. An assessment of the sensitivity of the results obtained to variation in measured resource use, effectiveness and/or unit costs will be undertaken using appropriate deterministic and probabilistic sensitivity analyses [38].

### Study duration

The study accrual period will be approximately 12 months. Each individual will be followed for 12 months.

### Sample size

A sample size calculation based on achieving 90% power at two-tailed type 1 error rate of 5% identified that 110 participants (55 participants per group) would be required to detect 10° of difference in ROM between the Maxm Skate program and standard care groups at three months after TKA assuming a within-group SD of 16°. The clinically significant difference in ROM of 10° and SD was estimated from parameters described by Mockford et al. [16], in which the effect of a physiotherapy regimen on ROM was measured over a one-year, post-TKA follow-up period. Furthermore, it is well established that daily activities, including climbing stairs and standing from a chair, require 90–120° of flexion, kneeling and squatting 110–165°, and 135° of flexion to lift from a bath [7–9]. However, patients rarely achieve > 120° of flexion post TKA and 110° of flexion is an optimal goal for rehabilitation following TKA [9–11]. Based on such awareness of requirements for daily activities, a 10° difference in ROM may delineate between the ability to climb stairs or kneel down in TKA patients.

In order to account for a potential 5% loss to follow-up, a total sample of 116 participants (58 per group) will be recruited.

### Statistical methods

All analyses will be conducted on an intention-to-treat basis and results reported in accordance with CONSORT guidelines [39]. The primary endpoint is the ROM at three months and differences between groups will be assessed using an independent two-sample t-test with log-transformation of the outcome, if necessary, in order to meet the assumptions of normality. If normality is not achieved using transformation, then the Mann–Whitney U test will be used. Differences between groups for the clinical performance tests (30-s Chair-stand and 4 × 10 m Fast Paced Walk Test) and data collected on scales such as the OKS will also be assessed using a two-sample t-test or Wilcoxon Rank sum test if normality is not achieved. Baseline characteristics, including ROM, will be accounted for in a sensitivity analysis using mixed effects models that will also account for any missing data. Where > 10% of data are missing, multiple imputation using chained equations will also be used. Functional evaluations that are assessed at multiple time points will also be assessed using mixed effects models with an interaction term between group and visit used to determine differences in group effects across time. Two-sided hypothesis tests will be performed for each outcome with a type-1 error rate of alpha = 0.05 used for determining statistical significance.

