**Methods:**

This is a single-blinded, randomised controlled trial (RCT) in which 116 eligible participants consented for primary TKA will be randomly allocated to receive either the Maxm Skate rehabilitation program or standard rehabilitative care. Fifty-eight participants per group will provide 90% power (α = 0.05) to detect 10° of difference in ROM between groups at three months after TKA, assuming a within-group standard deviation of 16° and allowing for 5% loss to follow-up. Participants randomised to the Maxm Skate group will use the skate device and accompanying iOS App and sensors to complete rehabilitation exercises, as outlined in the *Maxm Skate Rehabilitation Guide*. Outcomes will be compared to those receiving standard rehabilitative care.

A blinded physiotherapist will evaluate functional outcomes preoperatively and at 2, 4, 6, 12, 26 and 52 weeks after TKA. The functional assessment will include measures of knee ROM, pain, isometric knee strength, balance and knee/thigh circumference. Limited measures will also be assessed at day 2 postoperatively by an alternate, unblinded physiotherapist. Clinical outcome measures will be administered preoperatively and at 6, 12 and 52 weeks postoperatively. An economic evaluation will be conducted and participants will be screened for adverse event occurrences from the time of consent to 12 months postoperatively.

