### Randomisation and blinding

The randomisation schedule will be prepared using numbered and sealed, opaque envelopes. Participants will be randomly allocated in a 1:1 ratio to either the ‘Maxm Skate Rehabilitation Program’ or the ‘Standard Rehabilitative Care’ group. Block randomisation in groups of four will be used to ensure balance in the two groups. Randomisation will also be stratified by gender to ensure balance between groups for each gender. We note that the number of women undergoing TKA for osteoarthritis has been shown to be greater in Australia [21]. In addition, studies have demonstrated that there are differences between men and women in muscle and physical function recovery after TKA [22, 23].

The study will be single-blinded with blinding of study investigators but not participants. Participant randomisation to either Maxm Skate or Standard Care will be performed by the unblinded Study Coordinator, who will hold the treatment allocation code in confidence. The statistician will be blinded to the treatment allocation code when performing all analyses. Functional evaluations and performance tests will be conducted by a trained physiotherapist ([name]) who will be blinded to group allocation. This blinded physiotherapist will conduct all functional evaluations, excluding postoperative day 2, due to practical constraints. Non-blinded ward-based physiotherapists will conduct the day 2 assessments, as well as the preoperative Maxm Skate education session for participants allocated to the Maxm Skate group.

Due to the nature of the intervention there is a potential for participants to disclose, or physiotherapist to gauge, which group the participants are assigned. Participants will be educated and instructed not to advise the physiotherapist or treating surgeon of their group assignment at the time of their consent and randomisation with the unblinded Study Coordinator. However, if participants are concerned about their rehabilitative progress and feel it is necessary to discuss this with their treating surgeon, they will be able to do so. The breaking of blinding will be collected and reviewed during data analysis.

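### The primary t-test ignores baseline ROM and the gender stratum; the more precise adjusted model is relegated to a sensitivity analysis

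*Protocol article*

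**What the plan says.** The Statistical methods section of the protocol article sets the primary comparison of ROM at three months: "differences between groups will be assessed using an independent two-sample t-test". If normality fails, the outcome is log-transformed, and if that fails a Mann–Whitney test is used. No covariate enters. The chair-stand test, the walk test and scales such as the OKS get the same unadjusted treatment.

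Baseline ROM appears one step down: "Baseline characteristics, including ROM, will be accounted for in a sensitivity analysis using mixed effects models that will also account for any missing data". Multiple imputation is added when more than 10% of data are missing. The section also states: "All analyses will be conducted on an intention-to-treat basis".

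Under Randomisation and blinding, "Randomisation will also be stratified by gender to ensure balance between groups for each gender". Part of the reason given is that "studies have demonstrated that there are differences between men and women in muscle and physical function recovery after TKA". No analysis in the document names gender.

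The baseline value is collected anyway. The abstract says: "A blinded physiotherapist will evaluate functional outcomes preoperatively and at 2, 4, 6, 12, 26 and 52 weeks after TKA", and ROM is one of those functional outcomes.

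**The concern.** A preoperative ROM value that predicts three-month ROM explains part of the outcome variance. An unadjusted test leaves that part in the error term. The standard error is then larger than it need be, and any chance baseline difference between the arms stays in the headline estimate.

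Stratifying by gender balances gender across arms. If gender predicts ROM, an analysis that omits it still counts between-gender variance as noise in the comparison, so the interval is wider than the design warrants.

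A t-test at week 12 also uses only participants with a week-12 value. The analysis that uses the other visits of a participant who misses week 12 is ranked second. If the two analyses disagree, the less precise one gives the trial's answer.

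**Working it through.** **Inputs.** From Sample size: difference 10°, within-group SD 16°, two-sided 5%, 90% power, 55 evaluable per group, 5% loss, 58 per group recruited. Allocation is 1:1 (Randomisation and blinding). The document does not give r, the correlation of baseline with three-month ROM, so a range is assumed.

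**Reproducing the stated sample size.** The normal approximation gives n = 2 × 16² × (1.96 + 1.282)² / 10² = 53.8, so 54 per group. The exact t-test calculation gives 54.8, so 55. Allowing for loss, 55 / 0.95 = 57.9, so 58 per group and 116 in total. This matches the protocol. The stated size is that of the unadjusted test.

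**Effect of adjusting for baseline.** The residual SD is 16 × √(1 − r²). Power comes from the noncentral t distribution at 55 per group. The half-width is t(0.975, 108) × SD × √(2/55) = 1.982 × SD × 0.1907. The equivalent sample-size factor is 1/(1 − r²).

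| Assumed r | Residual SD | Power | 95% CI half-width | Sample-size factor |
|---|---|---|---|---|
| 0 (t-test) | 16.00° | 90.1% | 6.05° | 1.00 |
| 0.1 | 15.92° | 90.4% | 6.02° | 1.01 |
| 0.3 | 15.26° | 92.6% | 5.77° | 1.10 |
| 0.5 | 13.86° | 96.3% | 5.24° | 1.33 |
| 0.6 | 12.80° | 98.2% | 4.84° | 1.56 |

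**Chance imbalance.** With 55 per group, the 95% range of a chance difference in mean baseline ROM is ±1.96 × √(2/55) = ±0.37 SD. At r = 0.5, and taking the 16° SD, an imbalance at that limit moves the unadjusted estimate by 0.5 × 16 × 0.37 ≈ 3°, against a target of 10°.

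**Gender.** The document gives neither a gender difference in ROM nor a proportion of women. Trials with blocks of four stratified by gender were simulated at 110 participants, assuming 60% women (4,000 trials per setting).

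- *Assumed gender difference 10°.* Gender accounts for 10² × 0.6 × 0.4 = 24 of the 256 units of variance (9.4%). The type I error of the t-test was 0.040–0.043, against 0.051–0.053 for an analysis of covariance on gender and baseline. With r = 0, power was 91.0% against 92.1%.
- *Assumed gender difference 5°.* The share is 6/256 (2.3%), and the effect on type I error and power was negligible.

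**Missing data.** The planned 5% loss is 0.05 × 116 ≈ 6 participants. That is below the 10% trigger for imputation, so on the protocol's own expectation the primary t-test is a complete-case analysis.

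**The case against.** The strongest reply is that nothing here is an error. An unadjusted t-test is valid in a 1:1 randomised trial, the sample size was calculated for exactly that test, and power is 90.1%. The t-test's confidence interval already allows for chance imbalance. The adjusted model is planned, as are imputation above 10% missing and mixed models with a group-by-visit term for functional evaluations at several visits. The request is therefore only to change which analysis is called primary. The size of the benefit rests on an r that the document does not supply; at r = 0.3 it is 2.5 power points and 0.28° of half-width. The gender effect is small unless gender strongly predicts ROM, it errs on the conservative side, and the cited differences concern muscle and physical function, not ROM itself. Gender may also be among the baseline characteristics of the sensitivity model.

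All of this stands as a limit on size. It does not remove the point. The protocol fixes the ranking of the analyses, so this is not a detail left to the SAP, and the analysis ranked first is the one that uses less of the data collected. That the better model is already planned makes the change easier to adopt.

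One caution applies to the adjusted model. Recruitment and selection criteria places the baseline measures after randomisation. They are nevertheless taken before surgery by the blinded physiotherapist, and the protocol already intends to adjust for them.

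**Conclusion.** The concern holds as a matter of efficiency and precision, and should be acted on. The trial is not underpowered on its own assumptions and the t-test is not invalid.

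The loss ranges from close to nothing at r ≤ 0.1, through 2.5 power points at r = 0.3, to 6 points and 0.81° of half-width (6.05 − 5.24) at r = 0.5. Only at r = 0.5 is it equivalent to about a third more participants. All of these rest on an assumed r. Omitting gender makes the test mildly conservative if the gender difference in ROM is about as large as the 10° target, and matters little at 5°.

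The missing-data point is modest at the planned 5% loss, and no bias has been quantified. It does show that the primary analysis leaves out participants whom the mixed model would retain through their other visits.

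**What to change.** Reverse the order of the two analyses, and do so before unblinding so that the choice cannot depend on the results.

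- **Primary analysis:** a linear mixed model for ROM at the blinded postoperative visits (2 to 52 weeks), with baseline ROM, gender, visit and group-by-visit. The primary result is the group difference at 12 weeks, in degrees, with its 95% CI. The minimum acceptable version is an analysis of covariance of 12-week ROM on group, baseline ROM and gender.
- **Sensitivity analysis:** the unadjusted t-test.
- **OKS, KOOS, chair-stand and walk test:** the same adjustment, using each measure's own baseline and gender.

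An estimate in degrees also matches the 10° target and the economic outcome of cost per unit gain in ROM. The log-transform and Mann–Whitney fallbacks do not give a mean difference in degrees.

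The cost is wording in Statistical methods. No new data, visits or participants are needed. The 116 can stay; the sample size becomes conservative by an amount that depends on r.

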## Background

Primary total knee arthroplasty (TKA) is an increasingly common surgical intervention used to alleviate pain and physical dysfunction associated with end-stage degenerative joint disease. Following surgery, patients experience lower-extremity muscle weakness and commonly require physical rehabilitation to enhance functional outcomes and overall recovery [1, 2]. While TKA is a successful procedure for many patients, up to 15–20% of patients remain unsatisfied [3, 4]. Limited postoperative range of motion (ROM), which is often associated with arthrofibrosis, may be one factor associated with patient dissatisfaction. The recorded incidence of arthrofibrosis after primary TKA varies in the literature, in the range of approximately 1–13% [4–6]. When it occurs, it is a significant cause of patient dissatisfaction associated with poor ROM and is a causative factor of revision TKA [5, 6]. Therefore, as limited ROM is an early indicator of potential arthrofibrosis, rehabilitation that enables ongoing flexion/extension exercises and ongoing collection of such progress, may improve early detection of arthrofibrosis and as such appropriate rehabilitative management before the need for revision surgery. In addition, it is well established that daily activities including climbing stairs and standing from a chair require 90–120° of flexion, kneeling and squatting 110–165°, 135° of flexion to lift from a bath and > 150° for yoga or gardening [7–9]. However, patients rarely achieve > 120° of flexion post TKA and 110° of flexion is an optimal goal for rehabilitation following TKA [9–11]. At present, there are no universally accepted or widely implemented clinical guidelines available to consistently structure patient rehabilitation following TKA [12–14]. Consequently, rehabilitative protocols are not standardised and regularly based on institution-, surgeon- or occasionally, patient-specific preferences [1, 2, 12]. This lack of uniformity in the mode of rehabilitation results in therapy of different types, frequency, intensity and duration across sites and countries [1, 2].

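### A normality check decides whether the primary result is a difference in degrees, a ratio or a rank statistic, although the trial is sized on 10°

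*Protocol article*

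**What the plan says.** The Statistical methods section of the protocol article sets the primary analysis as a sequence. It begins: "The primary endpoint is the ROM at three months and differences between groups will be assessed using an independent two-sample t-test". The test is to be run "with log-transformation of the outcome, if necessary, in order to meet the assumptions of normality". The last step is: "If normality is not achieved using transformation, then the Mann–Whitney U test will be used". No criterion for normality is named, and no effect measure is attached to the second or third step. Adjustment for baseline ROM appears only in a sensitivity analysis with mixed models. Functional evaluations measured at several visits are also to be analysed with mixed models that include a group-by-visit term.

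The Sample size section works in raw degrees: the stated number of participants "would be required to detect 10° of difference in ROM between the Maxm Skate program and standard care groups at three months after TKA", with an SD of 16°. It defends 10° as a gap that may separate one daily activity from another. The Background says that "patients rarely achieve > 120° of flexion post TKA".

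**The concern.** The data choose among three target quantities, so what the primary result measures is not known until the outcomes have been examined. Only the first route gives a number that can be set against 10°. A log t-test gives a ratio of geometric means, and the ratio that corresponds to 10° changes with the control-group level. Mann–Whitney as described gives a p-value and no difference in degrees.

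The log step is also a doubtful remedy for this outcome. A log compresses high values and stretches low ones, so it reduces right skew and increases left skew. If knee ROM has a limited upper end and a tail of stiff knees, the transformation moves the data further from normality and the sequence runs on to the rank test.

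At stake is whether the headline result can be read on the scale on which the trial was justified, and whether that scale was fixed in advance.

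**Working it through.** **1. The article's own figure.** Inputs from the Sample size section: difference 10°, SD 16°, two-sided 5%, power 90%, 5% loss.
- Normal approximation: n = 2 × (1.960 + 1.282)² × 16² / 10² = 53.8, so 54 per group.
- Noncentral t: 54.8, so 55 per group, with power 90.1%.
- Loss: 55 / 0.95 = 57.9, so 58 per group and 116 in total.

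The stated sample size reproduces, and it belongs to a t-test on raw degrees.

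**2. What 10° becomes on each route.**
- t-test: 10°.
- Log t-test: (c + 10)/c for control level c, which is 1.11 at 90°, 1.10 at 100° and 1.09 at 110°. No single ratio corresponds to 10°.
- Mann–Whitney: P(X < Y) = Φ(10 / (16√2)) = Φ(0.442) = 0.67 under normality.

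**3. What the log does to skewness.** Shapes are assumed, with SD 16° and means of 100° and 110°.
- Normal: 0 becomes about −0.5.
- Bounded at 140° (beta): −0.45 becomes −1.00 at mean 100°, and −0.72 becomes −1.26 at mean 110°.
- Reflected gamma: about −1.0 becomes −2.0 to −2.2.
- Right-skewed gamma: +1.0 becomes about +0.5.

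The log helps only in the last case.

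**4. Which test becomes primary.** Simulation with 55 per group and SD 16°. Shapiro–Wilk at 5% on pooled within-group residuals is assumed, because the article names no check.

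| Assumed shape | Share ending at Mann–Whitney |
|---|---|
| Normal | about 3% (t-test kept in 95%) |
| Skewness −0.3 | about 20% |
| Skewness −0.6 | about 55% |
| Skewness about −1.1 | about 99% |

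The bounded beta gave 48% with no group difference and 72% with a 10° difference. Under the left-skewed shapes the log step was selected in essentially none of the trials. Under right skew of +1 it was selected in about 40%, and Mann–Whitney in 56–57%.

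**5. Error rates.**
- Whole sequence: type 1 error 4.7–5.6%, power from 90% to about 95%.
- Plain t-test on degrees, non-normal shapes: type 1 error about 5%, power 90–91%.
- Log t-test used alone under left skew: power about 83–88%. The sequence almost never stops there, so this is not the power of the planned procedure.
- Strongest left skew: the rank test reaches about 95%, against about 90% for the unadjusted t-test.

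**6. Power of an adjusted model.** Assume a correlation of 0.5 between baseline and three-month ROM; the article gives none. The residual SD is 16 × √(1 − 0.25) = 13.9°, and 10 / 13.9 = 0.72. With 55 per group the noncentrality is 0.72 × √(55/2) = 3.8, which gives about 96% power for normal data. Simulation under the strong left skew gives about 97%. Simulation error and the way the correlation is built can move that by a point or two.

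**The case against.** **Left skew is inferred.** A reader might conclude that Mann–Whitney is almost certain to become the primary test. The article does not support that. With SD 16°, a plain normal distribution puts 13% of patients above 120° at a mean of 102°, 11% at 100° and 6% at 95°. A strongly left-skewed model with a 130° ceiling and mean 102° puts 9.6% there. The Background statement cannot tell these apart, so the 99% is the top of a range that starts at 3%. This objection stands.

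**Inference is not damaged.** A reader might infer inflated type 1 error or an underpowered trial. The simulations show neither. Under strong skew the planned sequence has more power than the unadjusted t-test. This also stands.

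**Degrees are available elsewhere.** The repeated-measures mixed model can yield a 12-week contrast in degrees, and a Hodges–Lehmann shift could accompany the rank test, perhaps in an analysis plan that is not shown. This stands in part. These would be additional results, whereas the article itself names the sequence as the analysis of the primary endpoint. That is a stated rule and not a missing detail.

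**Two tempting extensions fail.** The Economic evaluation section says "The primary outcome will be the incremental cost per unit increase in knee ROM", and one might infer that this ratio could not be computed. However, it is a separate evaluation, nothing ties its ROM increment to the primary test, and a mean difference can be calculated whichever test supplies the p-value. One might also argue that a log is undefined for extension at 0° or below. The article does not say that extension will be log-transformed, and its rationale for 10° is in terms of flexion.

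**Conclusion.** The point holds as a matter of effect measure and pre-specification. The article ties the primary endpoint to a sequence whose result may or may not be in degrees, while its sample size and clinical rationale are entirely in degrees. How often the result would leave the degree scale depends on a distribution that the article does not report: from about 5% of trials if ROM is normal (3% Mann–Whitney, the rest log) to nearly all under strong left skew. The log step is useful only under right skew, which is not the direction that the Background suggests. The check buys little, since the plain t-test holds about 5% error and 90% power at this sample size across the shapes tried.

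The sample size is correct, and neither type 1 error nor power is materially harmed. The figures rest on the assumed shapes, SD 16°, 55 evaluable per group and a Shapiro–Wilk check. This should be corrected, but it does not threaten the validity of the trial.

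**What to change.** Make the primary analysis one linear model on untransformed ROM at three months, adjusted for baseline ROM and for gender (the stratification factor). Report the mean difference in degrees with a heteroscedasticity-robust or bootstrap 95% CI, whatever the distribution looks like. Delete the normality check and the log step. Keep Mann–Whitney as a named sensitivity analysis. The same change for the OKS and the performance tests is optional.

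The cost is wording only. Baseline ROM is already collected, gender is already a stratification factor, and 116 participants still suffice. The one statistical price is that, under strong left skew, a rank test beats the unadjusted t-test by about 5 points of power (95% against 90%). Baseline adjustment recovers this, at about 97% if the correlation is 0.5. The change should be made before allocation is unblinded, so that the choice of effect measure cannot appear to be driven by the results.
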